## Abstract

**Background:**

Overweight and obese children are likely to develop serious health problems. Among children in the U.S., Latino children are affected disproportionally by the obesity epidemic. Niños Sanos, Familia Sana (Healthy Children, Healthy Family) is a five-year, multi-faceted intervention study to decrease the rate of BMI growth in Mexican origin children in California’s Central Valley. This paper describes the methodology applied to develop and launch the study.

**Methods/Design:**

Investigators use a community-based participatory research approach to develop a quasi-experimental intervention consisting of four main components including nutrition, physical activity, economic and art-community engagement. Each component’s definition, method of delivery, data collection and evaluation are described. Strategies to maintain engagement of the comparison community are reported as well.

**Discussion:**

We present a study methodology for an obesity prevention intervention in communities with unique environmental conditions due to rural and isolated location, limited infrastructure capacity and limited resources. This combined with numerous cultural considerations and an unstable population with limited exposure to researcher expectations necessitates reassessment and adaptation of recruitment strategies, intervention delivery and data collection methods. Trial registration # NCT01900613.

**Trial registration:**

NCT01900613.

## Background

Despite recent evidence suggesting slight declines in low-income, child obesity rates in the United States, these trends are not shared equally across subpopulations and high rates of childhood obesity are still prevalent across the United States [1]. Based on the most recent National Health and Nutrition Examination Survey (NHANES), approximately one in six children and adolescents in the U.S., aged 2–19 y, are obese [2]. The prevalence of obesity disproportionately affects certain U.S. ethnic groups, including Latino-Americans. Among children and adolescent populations, obesity affects 21.2% of Latinos compared to 14% white non-Latinos [2]. Such differences suggest that more information is needed to assess childhood obesity risk and preventive factors in order to create culturally appropriate and sustainable behavioral interventions for high-risk populations.

Scant data exist on the efficacy of school- and community-based interventions targeting obesity prevention and healthy lifestyles for Latino children, resulting in a critical gap in understanding how multifaceted interventions impact behavioral change in these communities [3]. While nutrition education interventions targeting Latino parents of young children have reported improvement in Body Mass Index (BMI), it is unclear whether these approaches can be scaled-up and achieve sustainable results [4,5]. *Aventuras para Niños*, a community-based study conducted in San Diego, did not find significant improvement in BMI z-scores over the three-year follow-up study [6]. Although the San Diego study included family- and community-level components, additional economic incentives, for example similar to that used in the United States Department of Agriculture’s (USDA) Women, Infant and Children (WIC) program, may be needed to overcome financial barriers to achieving a healthy diet and lifestyle.

In attempt to address the dearth of literature in the field of childhood obesity prevention for the growing Latino community and data suggesting that underlying community factors may impact these rates, we develop *Niños Sanos, Familia Sana* (NSFS), a five-year multifaceted intervention study targeting California’s Mexican-origin communities. The research goals include (a) identifying individual and environmental factors that influence food consumption patterns; and (b) generating new knowledge about community- and school- based interventions to reduce the rate of growth of BMI within Mexican-origin children. The behavioral intervention includes curriculum-based interventions in the community (preschool) and schools (K-2). A companion parent education and market-based (fruit and vegetable vouchers) intervention addresses the reality that parents make food choices for young children but may not have the resources to make healthy choices.

This study includes a novel interdisciplinary theoretical model to explain the stages of, and influences on, behavioral change within the targeted community. To design the intervention, we integrate social cognitive theory (SCT) and an economic behavioral approach within the Health Belief Model (HBM) [7,8]. These models and theories enable us to focus on behavioral changes through multiple levels of influence, such as the individual, interpersonal and community levels [9]. The introduction of the economic behavioral assumptions within the context of the SCT and HBM is novel. Based on the interdisciplinary theoretical approach, we shifted away from a single intervention to a multifaceted intervention approach to explore the capacity for behavioral changes. To our knowledge this intervention approach is unique, as school-based and other community-based studies targeting the Mexican-origin population to date have focused on single and/or short-term interventions to create behavioral changes. Recent literature suggests that successful interventions must take place in a community setting that calls upon the involvement and “buy-in” of all stakeholders within that setting [10]. This approach addresses the problem of Mexican-origin childhood overweight/obesity within the context of a local community and allows us to partner effectively with the school and community, facilitating better awareness of the problem among all stakeholders. It also fosters participants’ abilities to work with us in tailoring the proposed interventions to meet their cultural, social and economic needs. Since this interdisciplinary model employs a community-based participatory research (CBPR) approach, input is required at all stages of school and community engagement, as well as in the development and implementation of the proposed interventions [11-15]. Thus our intervention is based in the local schools, community centers, food markets and health clinics.

A major goal of *Niños Sanos, Familia Sana* is to reduce the rate of growth of childhood obesity among Mexican-origin children between the ages of three and eight by improving the economic capacity of low-income, Mexican-origin families, enhancing the nutritional skills of families, supporting the capacity of schools to more effectively provide Physical Education (PE) opportunities for children in preschool and K-2 settings, and providing community art programs that allow for nutrition and positive behavioral health messaging. Biannual anthropometric data, annual physical activity data and annual household survey data are collected of our sample population, which allow us to determine the impact of behavioral and community intervention factors on rate of growth of childhood obesity within our study population. These data are compared to our comparison community that receives a non-nutrition community-based intervention.

## Methods

### Project design

The quasi-experimental design of this five-year intervention study allows us to match two communities in California’s Central Valley with similar demographic characteristics. Both towns are over 80% Mexican-origin and the targeted school communities are predominantly Mexican origin. The primary employment base is agricultural, and the community members have similarly low levels of educational attainment. Two additional essential criteria for the project are local community leadership involvement with the University of California, Davis (UCD) research team and no active comprehensive nutrition intervention present in either town. Based on these criteria and after completion of detailed environmental scans to ensure close community matching, the towns of San Joaquin and Firebaugh located in Fresno County, California (Figure 1) are selected, including their respective school districts Golden Plains and Firebaugh-Las Deltas. Prior to initiation of this research study, the UCD research team cultivated a relationship of mutual trust and respect in each town over the course of a year through a series of targeted meetings with community leaders including city managers, local elected officials, school superintendents and boards, teachers, religious leaders, parents and local health care professionals. The research team presented the proposed research at town hall presentations in each site to introduce and explore the project concept and receive feedback from community participants. Once the key community stakeholders agreed on project participation, the intervention and comparison community were randomly selected. Throughout the process of community engagement, a major goal of the research team is solidification of community understanding of the project by key actors, and establishment of clear communication and agreements among community leaders. In order to facilitate this process of community participation, a Community Advisory Council (CAC) of stakeholders from each community was recruited for the project in consultation with the university research team. Both councils include the following representatives: city manager, school superintendents, teachers, principals, school nurses, food service managers, representatives of the local health facility, religious leaders, community health outreach workers (*promotores*), and representation from a major local supermarket. Local *promotores* are employed to assist with broad based outreach and recruitment for all town hall and community events. Throughout the duration of the project, the CAC meets quarterly with the research team and members are invited to participate in all community events.

**Figure 1 F1:**
[figure not shown]
Map of California highlighting Fresno county.

The five-year study design allows for the first year to be used as a planning and start up year, which is critical for piloting all interventions and study instruments prior to implementation. In addition, this baseline year is critical for recruitment of households with eligible children. In both instances, input from the CACs is critical to provide recommendations to enhance recruitment strategies and participation of eligible applicants into the study.

### Subject eligibility and recruitment

*Promotores* are hired in both communities to facilitate recruitment of families and trained to conduct recruitment events and go house to house to recruit hard-to-reach families. Subject eligibility for this project is determined a priori by the USDA’s National Institute of Food and Agriculture (NIFA) guidelines stated in the request for proposal. Eligible applicants for the study include children who fall within the ages of 3 to 8 years of age during the intervention period years. During the first year of the study, families with children between the ages of 2–5 are recruited as these individuals are within the guideline requirements (Table 1).

**Table 1 T1:** Inclusion and exclusion criteria for family participation in NSFS study

**Criteria**	**Description**
Inclusion criteria:	• Have at least one child residing at home in the required age/grade level range. Children must be born between December 3, 2004 and October 1, 2009, or must be in 2nd grade or lower during the 2012–2013 school year and
	• Residence in the Firebaugh Las Deltas Unified School District (FLDUSD) or the Golden Plains School Unified District (GPUSD)
Exclusion criteria:	• Family/child not interested in participating or
	• Moved out of school district or
	• Child no longer living at home or
	• Not enough time to participate in required activities

To facilitate recruitment, all children in the same grade are recruited to meet ethical considerations of equal access to students from the same classroom. Children and their families are excluded if they are not interested in participating in the study, they move out of the district; they no longer have an eligible child living in their home, or do not comply with the completion of all survey instruments and anthropometric measurements. Families living within the Firebaugh-Las Deltas Unified School District (FLDUSD) are considered as the intervention group and those living in the Golden Plains Unified School District (GPUSD), which includes the town of San Joaquin, are considered participants in the comparison site.

Due to participants living in isolated communities with limited exposure to outsiders and the mixed immigration status of community members, developing trust between the research team and community members is important to allow for effective family recruitment and participation. A locally visible site location within the intervention community with Spanish-speaking staff is critical to project implementation. In addition, Spanish-speaking university researchers and students assist with participant recruitment. Several recruitment approaches are utilized including: (1) door-to-door recruitment (2) meet and greet events, (3) one-on-one/personal networks, (4) school events (back to school nights, child pick up drop off intervals), (5) Parent Teacher Meetings, (6) open market or *remate* informational booths, (7) community events (e.g., Day of the Dead, Red Ribbon Week), (8) religious organizations, and 9) community health fairs. In order to improve participation, food and raffles are offered. A master information sheet of all recruited families is used to track eligible, ineligible, refusal and dropout families. In order to track the completion of required activities for each family, an activity-tracking log records the progress. Each family must complete baseline surveys and anthropometric measures in order to join the program intervention activities in both sites.

Upon approval by UCD’s Institutional Review Board (IRB) of all data collection procedures and instruments, informed consent is obtained from legal guardians of eligible children, including fathers, mothers and/or grandparents. Informed consent is obtained through two primary methods: (1) face to face verbal review of all documents at the study field office or at participants’ homes, or (2) group presentations at the field office in the intervention site or at community events in the comparison site. A presentation is used for both individuals and groups in order to accommodate low literacy among participants and to facilitate better understanding of the research and assist in the consent process.

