#### Nutrition

The nutrition intervention consists of two components a) family nights and b) a school-based program. Family nights are led by a local health educator and are based on a series of focus groups to understand community perceptions of childhood obesity including barriers, opportunities, interpretation and prioritization of key prevention messages recommended by the American Academy of Pediatrics [34]. The nutrition team consists of University of California, Cooperative Extension (UCCE) nutrition staff, advisors and specialists; UCD faculty and graduate students; and local staff based in Firebaugh. Based on focus group data and findings from other studies, the team develops a three-year plan for family nights, including key messages, recommendations on logistical issues (space, length of classes), and a plan for evaluation. In this study, cultural adaptation begins with nutrition curricula and approaches that work well in the general low-income audience served by UCCE. The local health educator who lives in the community is trained in basic nutrition, safe food handling, adult education and learner-centered delivery techniques and meets with the nutrition specialist each month to modify messages and activities. Adapted lessons are piloted with one group of participants to incorporate group feedback before delivering the lesson to the rest of the families. Each lesson is approximately one hour in duration and includes facilitated discussion, a hands-on activity (such as label reading or meal planning), and a food demonstration and tasting of a recipe containing fruits and/or vegetables. Families are required to attend at least five of the ten classes offered each year (15 minimum over three years) to remain in the program. Any adult member of each eligible family can participate in the family nights to receive credit for attendance.

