#### Economic

The economic intervention consists of providing participating families in Firebaugh with monthly fruit and vegetable vouchers worth $25/month. Participating families receive the monthly payments throughout the three-year intervention period. This approach provides incentives to families to purchase more nutritious and healthier foods. Vouchers are allocated per family regardless of the number of eligible children, family size or composition. A “family” for voucher purposes is described as an eligible child and a guardian, and the members directly related to them who consume food using the same resources. The list of fruits and vegetables that families can purchase using their vouchers matches the list of fruits and vegetables used by the WIC program. Unused voucher money expires at the end of the month and the card is automatically reloaded. Vouchers can only be used at the Firebaugh Supermarket and market staff are responsible for ensuring that funds are spent on approved purchases. Families must attend nutrition classes or check-in with the NSFS staff on a monthly basis to continue receiving funds. If a family does not check-in during a given month, their card is frozen until they regain contact with program staff. This ensures that the cards are still within the participant’s possession and have not been lost or stolen. Additionally, NSFS staff collect food purchase receipts from participants on a monthly basis and transfer these receipts to the UCD team for processing.

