## Discussion

Careful consideration and strategies are required to maximize recruitment and retention of this hard to reach population of both the intervention and comparison communities. An important consideration is that farm work employment peaks during the months of April to October when many family members work long hours in the field. Strict adherence to using *promotores*, local staff, and/or field researchers to contact participants is required to contact participants to conduct informed consent, surveys and medical measurement. Further, relying on standard appointments for participants does not guarantee they show up at appointment time. It is therefore often required that program staff make visits to the families’ homes to conduct recruitment and/or data collection procedures. In addition, program staff works with the school nurse to schedule anthropometric measurements of children during the school day.

Recruitment and retention of participants for the comparison community of San Joaquin also presents a unique set of challenges. For example, the comparison site lacks office space that would provide visibility to the project in that community. Because of funding limitations, project staff use space available from local organizations such as churches and the community center. This may compromise the stability of staff access to the community at large in the comparison community. Also, since there is no active nutrition intervention in San Joaquin, project staff anticipated more problems with recruitment and retention. Therefore, focus groups were used to develop a series of workshops that focus on family well-being and ways in which parents can support their children’s education. These will be offered monthly to all community members. Workshop attendees invite other community members who are eligible to participate in the study. This strategy increases the community members’ interest in NSFS and the enrollment of participants.

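### Eligibility rules exclude families for events after enrolment, and the article does not say whether the class-attendance condition in the intervention town also ends outcome follow-up

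*Protocol article*

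**What the plan says.** The text under Subject eligibility and recruitment lists who is excluded. Besides families not interested in taking part, it names cases where "they move out of the district; they no longer have an eligible child living in their home". The list closes with a ground about completeness, which catches those who drop out of data collection: "or do not comply with the completion of all survey instruments and anthropometric measurements". Table 1 in the same section adds "Not enough time to participate in required activities".

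A separate sentence in that section sets the condition for starting: "Each family must complete baseline surveys and anthropometric measures in order to join the program intervention activities in both sites".

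The Nutrition section, describing the family nights in Firebaugh, sets this condition on participants: "required to attend at least five of the ten classes offered each year (15 minimum over three years) to remain in the program". The Economic section has a different condition for the voucher: "Families must attend nutrition classes or check-in with the NSFS staff on a monthly basis to continue receiving funds".

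For San Joaquin, the Discussion expects recruitment and retention problems "since there is no active nutrition intervention in San Joaquin", and describes family well-being workshops instead: "These will be offered monthly to all community members". No attendance minimum is given for them.

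Nowhere does the article say that a family excluded under these rules is still measured, or is analysed in its town of enrolment.

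**The concern.** The primary comparison is BMI growth in the two towns after three years. An eligibility criterion should be settled at entry. Several of these are settled later, by what the family does during follow-up. Removing children on that basis means comparing selected families, and a larger sample does not cure that. It also discards valid heights and weights because, say, a food-frequency questionnaire was missed.

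A rule printed for both towns can still select differently in each. Firebaugh has a field office and vouchers that depend on monthly contact. San Joaquin has neither, and the authors expected more retention difficulty there. If the class minimum also ends follow-up, the rules themselves differ by town, and the intervention group would be filtered on engagement with the intervention.

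**Working it through.** **Step 1. Is each rule settled at entry or later?**

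- *Moving away.* Residence in one of the two districts is already an inclusion criterion, so moving out can only be a later event.
- *Child no longer at home.* The same holds, because a resident child is an inclusion criterion.
- *Incomplete surveys or measurements.* The rule covers all instruments and is not limited to baseline. The condition for joining is stated separately. Table 2 repeats anthropometry, food security and the food-frequency questionnaire every 6 months, and the household survey and medical history yearly. The natural reading includes follow-up, though the article does not say so outright.
- *Not enough time.* This may partly be refusal at recruitment, but as worded it can also apply later.
- *Class minimum.* This is a later event by construction, stated only for the intervention. It refers to staying in the programme, and class attendance is in neither exclusion list.

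**Step 2. The plan's own figures.** Inputs from Sample size calculation: about 400 children per group, 0.20 SD, 80% power. Two-sided alpha of 0.05 is assumed, as the article gives none.

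- n per group = 2(1.960 + 0.842)² / 0.20² = 393, against about 400 stated.
- Detectable difference at 400 = 2.802 × √(2/400) = 0.198 SD.
- Design effect = 1 + (143 − 1) × 0.01 = 2.42; √2.42 = 1.556 (stated 1.56); 1.556 × 0.20 = 0.311 SD.

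These reproduce. The only loss figure given is mobility below 5%. A 5% loss leaves 380 per group and 78.7% power before clustering. Nothing is allowed for exclusion through non-completion or low attendance.

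**Step 3. What removal from one town would do (assumed inputs).** Let a share q of one town be removed, and let their children's mean change differ by d from the rest, regardless of the intervention. The full-town mean is m + q·d and the retained mean is m, so the shift is q·d.

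- q = 25%, d = 0.20 SD: 0.25 × 0.20 = 0.05 SD, a quarter of the 0.20 SD target.
- q = 10%: 0.02 SD. q = 50%: 0.10 SD.

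The sign follows the sign of d, which the article does not give.

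A second formulation removes the least compliant share q when compliance correlates ρ with BMI z-score change: bias = ρ·φ(z_q)/(1 − q). For q from 10% to 40% and ρ from 0.1 to 0.3, this runs from 0.02 to 0.19 SD. At q = 30% and ρ = 0.2 the bias is 0.10 SD. With no true effect, the two-sided false-positive rate is then about 25% unclustered, or 13% with the design effect of 2.42, instead of 5%.

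**Step 4. What the completeness rule could remove (assumed inputs).** Take baseline plus six 6-monthly rounds and assume 95% or 90% of children complete each round.

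- If misses are independent and one miss excludes for good: 0.95⁷ = 0.698, leaving 279 of 400; 0.90⁷ = 0.478, leaving 191. The detectable difference becomes 2.802 × √(2/279) = 0.24 SD or 2.802 × √(2/191) = 0.29 SD, before clustering.
- If the same families miss every round: 0.95 × 400 = 380 or 0.90 × 400 = 360 remain.

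The first case is pessimistic. Not every instrument is due at every round (acculturation is baseline only), and misses usually cluster within families.

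**The case against.** The strongest objection concerns the class minimum. A reader might infer that Firebaugh families below five classes a year are dropped from the study, and that the primary result is therefore biased in favour of the intervention. The documents do not support that. The Nutrition section speaks only of remaining in the programme, and neither exclusion list mentions attendance. The voucher can be kept by a monthly check-in without attending a class, and a lapsed card is frozen only until contact resumes. All this fits a condition on benefits at least as well as removal from measurement. Nor does the article establish that low attenders' children gain BMI faster; worried parents of heavier children might attend more. This objection stands, and it limits what can be said about a difference between the towns.

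It also stands that the other exclusions are printed for both towns, that San Joaquin's lack of a stated minimum may reflect condensation, and that the losses in Step 4 depend on an exclusion mechanism the article does not spell out.

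Two further objections carry less weight. The completeness rule might mean baseline only, since it sits under recruitment and similar wording is used for joining. But baseline completion has its own sentence, the instruments recur, and the neighbouring exclusions for moving or a child leaving home cannot be baseline events. It can also be said that analysis sets belong in an unseen SAP. That would answer a complaint about missing detail, but here the article itself prints the exclusion rule, and the rule is what needs changing.

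**Conclusion.** The point holds in a limited form. As printed, the eligibility section excludes families for events after enrolment. Following it would restrict the three-year comparison to families selected on later behaviour and would lose usable BMI data. That rests on the text alone, with the one reservation that the completeness rule is not expressly tied to follow-up.

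The class minimum is a conditional concern. If it ends outcome follow-up, retention rules differ by town and the comparison can be biased in either direction. If it ends only programme benefits, it does no harm to the comparison. The article leaves this open.

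No bias estimate can be taken from the document. The 0.05 SD shift against a 0.20 SD target is an illustration with an assumed 25% removed and an assumed 0.20 SD difference; the wider ranges above are equally assumed. The planned sample size is not in dispute. The matter is worth settling early: the Trial status section says the intervention has begun, and BMI values not taken cannot be recovered.

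**What to change.** - State that programme participation and outcome follow-up are separate.
- Keep every enrolled child with a baseline BMI in the primary analysis, by town of enrolment, whatever the class attendance or survey completion.
- Continue the 6-monthly BMI measurement for low attenders and for families with incomplete surveys who still live in the district. For those who move, use all BMI values up to loss.
- Take moving, non-completion and lack of time after enrolment out of the exclusion criteria, and list them as recorded reasons for discontinuation. Keep refusal at recruitment as a separate category.
- Reconcile the eligibility, Nutrition and Economic sections on what falling below the class minimum ends. This point does not ask for the attendance condition itself to change.
- In the same edit, reconcile Study instruments, which mentions nutrition workshops in the comparison group, with the Discussion, which describes none. Neither sets an attendance minimum there.

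The cost is mostly wording, plus some tracking and measurement. Children are already measured at school, at health fairs, at the study office and at home, and dropouts are already logged. Home visits are often needed, however, so the extra work is not nil. The estimate may also turn out less favourable.
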